#### Therapeutic clothing

The control group will receive Binamed® therapeutic clothing without antimicrobial agents (BAP Medical). This is therapeutic clothing made of micro-modal and lycra. Micro-modal is a semi-synthetic wood cellulose fiber. This fiber has a high strength and elasticity and high moisture permeability.

The intervention groups receive either DermaCura® antimicrobial clothing (D&M) (group B) or Binamed antimicrobial therapeutic clothing (BAP Medical) (group C). DermaCura® antimicrobial clothing (D&M) is made from 98% TENCEL® C and 2% elastane. Chitosan (1%) is added to TENCEL ® C. Binamed antimicrobial therapeutic clothing (BAP Medical) consists of micro-modal lycra and woven silver filaments.

Patients will receive three sets of therapeutic clothing at the beginning of the study. During the study, three additional sets of therapeutic clothing can be requested by patients. Each set consists of a shirt with long sleeves and trousers. Socks and gloves can be prescribed if necessary. During the study, usual care (including the application of emollients, topical corticosteroid ointments, or creams only if needed and/or antihistamines) is continued according to the treatment guidelines of AD [10]. When AD worsens, the frequency and class of topical steroid treatment can be increased (as is usual care in the Netherlands). In case of a severe exacerbation requiring UV therapy or systemic treatment with immunosuppressive medication, participation in the study is stopped.

Measurements and assessments will be performed at baseline (start of intervention) and 1, 3, 6, and 12 months after baseline, as this reflects clinical practice. In addition, participants are requested to answer a weekly questionnaire on the use of therapy, AD symptoms, and costs. See Additional file 1 for an overview of the Standard Protocol Items: Recommendations for Interventional Trials (SPIRIT) 2013 checklist items. See Fig. 2 for the SPIRIT diagram of the trial procedures.

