### Sample and laboratory procedures

In this study, bacterial swabs from the skin are obtained by a trained research assistant wearing non-sterile gloves. Sterile Copan MSwabs are used and samples will be collected for analysis of *S. aureus* colonization.

At the baseline assessment, swabs are taken from an affected part of the skin, preferably of the antecubital, popliteal, or neck fold. At all following visits, the swabs are taken from the same site. The skin surface is swabbed for 30 s.

Regarding the silver-coated textiles, there is a theoretical possibility for the adsorption of silver from the garment through the skin [19]. Therefore, silver excretion is assessed in urine in this group only. Morning urine of participants able to urinate in a urine cup will be collected and sent to a specialized laboratory. The urine of participants in the other groups will be collected as well in order to ensure that patients remain blinded.

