#### Secondary outcomes

Secondary outcomes include physician- and patient-reported effectiveness, degree of impetiginization, patient-reported quality of life, *S. aureus* colonization, use of topical corticosteroids and antibiotics, cost-effectiveness, and safety. Figure 2 provides an overview of the measurements per visit.

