### Physician-reported outcomes

The effectiveness of the therapeutic clothing will be assessed by using the EASI and Investigator Global Assessment (IGA) [20] and IGA for impetiginization in atopic dermatitis. Eczema severity will be assessed by a blinded rater. EASI is a validated scale recommended by the Harmonising Outcome Measures for Eczema (HOME) initiative [21] as an outcome for eczema severity. The final EASI captures erythema, excoriation, edema, lichenification, and body surface area. The IGA impetiginization is an outcome measure for impetiginization in atopic dermatitis that still needs validation.

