### Topical corticosteroid use

The amount of topical corticosteroids (TCS) use will be derived from a weekly questionnaire. Participants are asked to fill out the number of days, frequency per day, and name of TCS that are used. The difference in the amount and TCS potency between groups will be compared as a marker for the effectiveness of the therapeutic clothing.

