### Cost-effectiveness

The economic evaluation of the clothing without antimicrobial agents (control group) and microbial growth reducing/antimicrobial clothing based on chitosan or silver (intervention groups) will be calculated as the incremental cost-effectiveness ratio (ICER). The primary effect outcome measures will be the effectiveness of the therapeutic clothing assessed by using the EASI for the cost-effectiveness analysis (CEA) and quality-adjusted life years (QALY) for the cost-utility analysis (CUA). QALYs will be measured for a 1-year period, based on the Dutch tariff for the EQ-5D.

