### Data collection, monitoring, and data analysis

ALEA will be used as a data management system [18]. Patient confidentiality will be ensured by using identification numbers. In a final stage, data from both management systems will be extracted to a SPSS dataset. Data management will be performed by the investigator and monitored by an independent monitor as predefined in the monitoring plan.

The data analysis will be conducted according to the intention-to-treat principle. The primary hypothesis is tested by means of linear mixed model analysis. The linear mixed model will use EASI as a dependent variable, and inclusion EASI, group, time, and time*group as independent variables; in addition, the EASI at baseline will be used as an additional covariate. As the time period between the visit varies (*t* = 1, 3, 6, and 12 months), time is defined as a continuous variable, in which we calculate the number of months from baseline. A two-sided alpha of 0.05 is used. Secondary outcome parameters will also be analyzed with linear mixed models. No interim analysis is planned, due to the low risks of participating in this study. Data will be available upon request.

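### One linear mixed model is fixed for the secondary outcomes whatever their scale, which can mislead for yes/no outcomes and for skewed topical steroid amounts

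*Protocol article*

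**What the plan says.** In the protocol article, Data collection, monitoring, and data analysis, the primary model has EASI as the response and "inclusion EASI, group, time, and time*group as independent variables", with time continuous in months. The same paragraph adds: "Secondary outcome parameters will also be analyzed with linear mixed models". No exception by type of outcome follows, and no logistic, ordinal, count, two-part or transformed model is named for any of them.

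The secondary outcomes are described in other sections:

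- Secondary outcomes lists, among others, *S. aureus* colonisation and "use of topical corticosteroids and antibiotics, cost-effectiveness, and safety".
- Physician-reported outcomes names the "Investigator Global Assessment (IGA) [20] and IGA for impetiginization in atopic dermatitis", and says that the second scale has yet to be validated.
- Sample and laboratory procedures: "Sterile Copan MSwabs are used and samples will be collected for analysis of" *S. aureus* colonisation. Whether the result is presence or quantity is not stated.
- Topical corticosteroid use: "Participants are asked to fill out the number of days, frequency per day, and name of TCS that are used". Amount and potency are then compared between groups as a marker of effectiveness.
- Therapeutic clothing describes usual care as including "topical corticosteroid ointments, or creams only if needed".

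Two listed secondary outcomes have descriptions of their own. Cost-effectiveness is an incremental cost-effectiveness ratio. Safety is registration of adverse events, plus urinary silver in the silver group only.

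**The concern.** A linear mixed model assumes a continuous response with constant residual variance. Read with the primary model, it also implies a straight line over 12 months. A proportion cannot go below 0 or above 1, and a steroid amount cannot go below 0, but a straight line can. Where many participants report no steroid use and a few report a lot, the variance changes with the mean, and a common-variance standard error can be too small when the arms differ.

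Two of the outcomes concerned carry weight in the trial's argument. Lower *S. aureus* colonisation is the mechanism that the Background gives for the clothing. Steroid use is the plan's own marker of effectiveness, and because topical treatment may be stepped up when the disease worsens, a benefit could show as less steroid rather than lower EASI. An unreliable interval on steroid use would make the EASI result harder to explain.

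**Working it through.** **1. The plan's own figure.** The only figure to reproduce is the primary sample size. Inputs from Sample size: difference 6.6, SD 13, correlation 0.6, two-sided alpha 0.05, power 0.80, 20% loss.

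- Effect size: 6.6/13 = 0.51, as stated.
- Variance factor for the mean of four post-baseline visits: (1 + 3 × 0.6)/4 = 0.70.
- The t-based calculation gives 44 per group; 44/0.80 = 55; 3 × 55 = 165, as stated. The normal approximation gives 43, then 54 after loss (162 in total).

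The sample size reproduces and does not depend on the secondary models.

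**2. Simulation of the stated model on other scales.** Taken from the plan: 44 completers per arm, visits at 1, 3, 6 and 12 months, the stated model, and correlation 0.6 (applied to an underlying latent scale). Assumed, because the article gives none of it: a random intercept, prevalences of 30 to 95%, five ordinal grades, zero-share settings of 0.3 and 0.6, and effect settings of 0.5 and 1.0 (0.5 only for the ordinal scale). Results are for one active arm against control at 12 months, with 1,000 to 1,500 runs per case.

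| | Yes/no | Ordinal | Zero-heavy amount |
|---|---|---|---|
| Rejection, no effect | 4.2–5.6% | 5.2% | 5.7–6.4% |
| 95% interval coverage, with effect | 92.3–96.3% | 93.5% | 85.8–92.5% |
| Model SE / true SD, with effect | 0.90–1.06 | 0.96 | 0.75–0.90 |
| Fitted values out of range, all settings | 0–26.4% | 0% | 1.9–26.8% |
| Arm-mean intervals crossing the scale limit, all settings | 0–78.0% | 0% | 12.8–96.8% |

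With 1,000 runs, the simulation error on a 5% rate is √(0.05 × 0.95/1000) = 0.7 percentage points, so 6.4% is about two such errors above 5%.

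The yes/no results depend on position. At 50% and 70% prevalence with no effect, nothing left the range. At 95% with no effect, 4.4% of fitted values and 63.8% of arm-mean intervals did. The worst case started at 30% with a mean difference of −0.234, which leaves the active arm near 0.30 − 0.234 = 0.07.

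Limits: coverage was measured around the mean estimate, so bias is not assessed. The 95% prevalence case with an effect was not obtained, because a data set had no variation in the baseline covariate.

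**3. Does unequal binary variance alone give a wrong standard error?** The variance p(1 − p) is 0.25 at 50% and 0.09 at 90%, a ratio of 2.8. Take one visit, equal arms of size n, and compare a 50% arm with a 90% arm:

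- True variance of the difference: (0.25 + 0.09)/n = 0.34/n.
- Pooled over those two arms: 2 × 0.17/n = 0.34/n, which is identical.
- Third arm at 50%: pooled variance (0.25 + 0.25 + 0.09)/3 = 0.197; √(0.197/0.17) = 1.08, so the SE is 8% too large.
- Third arm at 90%: (0.25 + 0.09 + 0.09)/3 = 0.143; √(0.143/0.17) = 0.92, so the SE is 8% too small.

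For the two arms that differ, the error is nil to about 8%. Two arms at the same level while the third differs are further off: √(0.197/0.25) = 0.89 for two at 50%, and √(0.143/0.09) = 1.26 for two at 90%. All of this needs a 40-point gap between arms.

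**The case against.** The strongest reply has three parts.

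First, this is one summary sentence in a journal article, and links, scales and transformations are commonly left to the analysis plan, which is not shown. That would answer a complaint of missing detail. It does not fully answer this one, because the sentence names a model family rather than leaving it open.

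Second, most of the data types are inferred. Only the IGA scales are clearly not continuous. The swab scale is not given, antibiotic use is named without a measure, and as-needed use makes zero steroid amounts possible without showing that they dominate. The steroid analysis unit is not stated either, and totals over months would hold fewer zeros than single weeks. This stands and limits what can be said about size.

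Third, the linear model is fairly robust here. Tests under no effect held close to 5%, ordinal estimates stayed on the scale, and a mean difference on a 0/1 outcome is simply a risk difference. This stands too.

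A reader might infer that every secondary outcome is caught, adverse events and cost-effectiveness included. The article describes both separately, and silver measured in one group cannot enter a group-by-time model. A reader might also infer that the model always gives wrong error bars, or that the 2.8-fold variance ratio proves it. The simulation and the pooled-variance arithmetic do not support that.

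**Conclusion.** The point holds in a limited form. The article fixes a linear mixed model without regard to scale, and for some of the outcomes it names that is a poor choice.

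- **Yes/no outcomes** (antibiotic use; colonisation if scored present/absent): out-of-range estimates are possible when an arm lies near 0 or 1. Coverage stayed near nominal.
- **Skewed steroid amounts with many zeros:** intervals can be too narrow when there is an effect, with coverage down to about 86% and model SEs as low as 75% of the true SD.
- **IGA and impetiginisation IGA:** the concern is interpretability. A mean difference treats the steps between grades as equal, and the article offers no support for that, least of all for the unvalidated scale. No error-rate problem was seen.

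The sizes rest on assumed prevalences, zero shares and effects, since the article gives none. The primary EASI analysis, the 55 per group, cost-effectiveness and safety are untouched.

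**What to change.** Replace the single sentence with a short statement by outcome type:

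- Keep linear mixed models for POEM, the VAS scales and the quality-of-life totals.
- Use mixed logistic models, reported as marginal risk differences, for antibiotic use and for *S. aureus* colonisation if it is scored present/absent.
- Use proportional-odds mixed models for IGA and impetiginisation IGA.
- Use negative-binomial or two-part models for steroid amounts. Robust or bootstrap intervals around the linear model are a simpler alternative; they address the interval width but not fitted values below zero.

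State the scale of the swab result and the period over which steroid use is totalled, since the choice of model turns on both. If the swab gives a quantity, the model should follow its distribution.

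No new data are needed. The cost is slightly more programming and possible convergence problems where categories are sparse, so a fallback should be named in advance. The change is best made before unblinding.

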## Discussion

The ABC study is a pragmatic randomized controlled multi-center trial that compares the effectiveness of antibacterial therapeutic clothing with non-antibacterial therapeutic clothing in patients with moderate to severe AD. This study will provide high-quality evidence to inform clinical practice whether or not antibacterial therapeutic clothing is effective for AD. In addition, the cost-effectiveness of antibacterial clothing will be evaluated.

This study will also provide useful insights in the treatment of AD during a longer period. Data concerning the use of topical corticosteroids, adherence to the clothing, and use of other therapy will be available for analysis. In addition, the fact that both children and adults will participate from five centers across the Netherlands will provide us with data that can be used to compare age differences and treatment differences across a semi-national level. In addition, this trial will be the first trial to monitor the safety of textiles with silver in patients with the abnormal skin barrier.

In conclusion, the ABC trial will assess the (cost-)effectiveness and safety of antibacterial therapeutic clothing with chitosan and silver over a treatment period of 12 months in patients with moderate to severe atopic dermatitis.

## Abbreviations

AD: Atopic dermatitis
EASI: Eczema Area and Severity Index
IGA: Investigator’s Global Assessment
POEM: Patient Orientated Eczema Measure
Pruritus VAS: Pruritus visual analogue scale
HRQOL: Health-related quality of life
*S*. *aureus*: *Staphylococcus aureus*
